**Study Proposal and Rationale**

Patients with metastatic cancer are generally treated with chemotherapy, which has improved median survival compared to best supportive care. Despite this, patients continue to have persistent disease at sites that were initially involved with cancer.

Radiation therapy is an effective modality for treating localized cancer but until recently has been only used for palliation of symptoms once a patient develops metastatic disease. However, there is a rapidly enlarging clinical experience of extracranial stereotactic radiation to aggressively treat metastatic sites. Since patients with metastatic disease clearly have systemic disease, there is an urgent need to integrate effective drug therapy with increasingly effective local therapy. Although, both extracranial stereotactic radiation and Sutent have favorable toxicity profiles, there are no clinical data on the combination. The goal of the phase I trial is to use increasing doses of extracranial stereotactic radiation therapy to all sites of involved disease in combination with increasing doses of Sutent in order to determine the dose limiting toxicity (DLT), and maximum tolerated dose (MTD). The goal of the phase II trial is to determine if the addition of radiation therapy and Sutent will improve progression-free survival and overall survival and at the minimum have a positive impact on quality of life, response rate and palliation of symptoms.

**3.** **TRIAL SCHEMA**

Determine eligibility

**↓**

| **REGISTER** | **Treatment** | Days  1-7 | 8-12 | 13-14 | 15-19 | 20-28 | 29-42 |
| --- | --- | --- | --- | --- | --- | --- | --- |
| XRT |  | X |  | X |  |  |
| Sutent | X | X | X | X | X |  |

**↓**

Additional chemotherapy (as determined by Medical Oncology)

**↓**

Maintenance Sutent (until death or progression) and appropriate follow-up

**Phase I Dose Levels**

| **Dose Level** | **Radiation Dose** | **Sutent Dose** |
| --- | --- | --- |
| 1 | 40 Gy in 10 fractions | 25 mg PO QD |
| 2 | 40 Gy in 10 fractions | 37.5 mg PO QD |
| 3 | 50 Gy in 10 fractions | 37.5 mg PO QD |
| 4 | 50 Gy in 10 fractions | 50 mg PO QD |
| 5 | 60 Gy in 10 fractions | 50 mg PO QD |

- Two weeks after completion of any chemotherapy, maintenance Sutent in 6 week cycles (consisting of Sutent 50 mg PO QD weeks 1-4 followed by no treatment weeks 5-6) until progression or death

**4.** **INCLUSION CRITERIA**

1. Histologically or cytologically confirmed diagnosis of cancer (including epithelial carcinoma, sarcoma, and melanoma)
2. Age 18 years or older
3. Life expectancy > 3 months
4. Patients with AJCC (6th edition, 2002) stage IV cancer with distant metastases and without pleural or pericardial effusion at diagnosis and before start of study
   1. Patients with pleural effusion that is transudative, cytologically negative,

and non-bloody are eligible

- 1. If a pleural effusion is too small for diagnostic thoracentesis, the patient will be eligible.

1. Patients with 1-5 sites of maximum tumor dimension (for each individual site) of ≤ 10 cm or < 500 cc volume and amenable to radiation therapy as seen on standard imaging (CT, MRI, bone scan, PET/CT)
2. Unidimensionally measurable disease (based on RECIST) is desirable but not strictly required.
3. Brain metastases must have been treated prior to enrollment on study, preferably with stereotactic radiosurgery or surgery.
4. Eastern Cooperative Oncology Group (ECOG) performance status ≤ 2 (Karnofsky ≥ 60%)
5. No prior radiation therapy to currently involved tumor sites
6. Room air saturation (SaO2) > 90%
7. Patients must have normal organ and marrow function as defined below:

Hemoglobin > 9.0 g/dl

Absolute neutrophil count (ANC)  1,500/l

Platelets  100,000/l

Total bilirubin within institutional limits

Albumin > 2.9 g/dl

Alkaline phosphatase < 2.5x upper limit of normal

AST and ALT <2.5 x upper limit of normal

1. Informed consent must be obtained from all patients prior to beginning therapy. Patients should have the ability to understand and the willingness to sign a written informed consent document.
2. Inclusion of Women and Minorities: Both men and women of all ethnic groups are eligible for this trial. The proposed study population is in the table below:

Table 2:

|  | White, not of Hispanic origin | Black, not of Hispanic origin | Hispanic | Asian or Pacific Islander | Unknown | Total |
| --- | --- | --- | --- | --- | --- | --- |
| Male | 24 | 4 | 6 | 2 | 0 | 36 |
| Female | 20 | 3 | 5 | 1 | 0 | 29 |
| Total | 44 | 7 | 11 | 3 | 0 | 65 |

1. Radiation therapy requirements: Patient must have a completed treatment plan approved by the protocol review team ([name] or [name] AND [name] or [name])

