**11. ADDITIONAL INTERVENTIONS – CHEMOTHERAPY, SURGERY AND/OR ADDITIONAL RADIATION**

11.1 Interventions prior to protocol therapy: If chemotherapy, surgery and/or radiation are recommended by the treating physicians based on the patient’s clinical needs, they may be performed two weeks before or after days 1-28 of protocol therapy.

For instance, a patient with a history of breast cancer status post mastectomy (three years ago) and adjuvant chemotherapy now presents with a solitary brain metastasis, a single lung lesion and two bone lesions. The brain metastasis and lung lesion are both amenable to resection. Subsequently, the patient receives whole brain radiation and taxane based chemotherapy. After chemotherapy, CT of the chest abdomen and pelvis and MRI of the brain reveal no evidence of metastatic disease but bone scan demonstrates residual uptake in the two bone lesions. Two weeks after completion of chemotherapy, the patient is eligible for protocol therapy. The patient will receive Sutent on days 1-28 and extracranial stereotactic radiation on days 8-12 and 15-19 as per protocol. Two weeks after protocol therapy (day 43), the patient may receive additional chemotherapy. After completion of all planned chemotherapy, the patient will start maintenance Sutent. Therefore, all of the chemotherapy, surgery and whole brain radiation are allowed by protocol but are not considered “on protocol therapy”. While all toxicities of these interventions will be documented and recorded, any toxicity resulting from non-protocol therapy will not count as dose-limiting toxicity.

11.2 If patients have documented progression during additional chemotherapy and/or maintenance Sutent, the patient will be taken off protocol. At that time, any necessary intervention (chemotherapy, surgery and/or radiation will be allowed).

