**13. MEASUREMENT OF EFFECT**

- Response and progression will be evaluated in this study using the new international criteria proposed by the RECIST Committee. (38) Changes in only the largest diameter (unidimensional measurement) of the tumor lesions are used in the RECIST criteria.
- All lesions (except lesions seen on bone scan alone) are considered to be target lesions and are measurable. They are defined as being accurately measured in one dimension (longest diameter to be recorded). All tumors must be recorded in millimeters (or decimal fractions of centimeters) using a ruler or caliper.
- Lesions seen on bone scan only are not measurable and therefore are evaluated separately
- All baseline evaluation should be performed as closely as possible to beginning of the treatment and never more than 4 weeks before the beginning of treatment.
- The same method of assessment and the same technique should be used to characterize each identified and reported lesion at baseline and during follow-up.
- First assessment should be performed 4-6 weeks after completion of radiation therapy.
- Response Criteria for all lesions (except lesions seen only on bone scan):
  - Complete response (CR): Disappearance of all lesions
  - Partial response (PR): At least 30% decrease in the sum of the longest diameter (LD) of all lesions, taking as a reference the baseline sum LD
  - Progressive disease (PD): At least a 20% increase in the sum of the LD of the target lesions, taking as a reference the smallest sum LD recorded since the treatment started or the appearance of one or more new lesions
  - Stable disease (SD): Neither sufficient shrinkage to qualify for PR or sufficient increase to qualify for PD, taking as reference the smallest LD since the treatment started.
- Response Criteria for lesions seen only on bone scan:
  - Complete response (CR): Disappearance of lesion.
  - Stable disease (SD): Persistence of lesion on bone scan.
- Evaluation of best overall response:
  - The best overall response is the best response recorded from the start of the treatment until disease progression/recurrence (taking as reference for progressive disease the smallest measurements recorded since the treatment started). The patient’s best response assignment will depend on the achievement of both measurement and confirmation criteria:

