  - All patients who have met the eligibility criteria will be included in the main analysis of the response rate. Patients in response categories 4 – 8 will be considered as failing to respond to treatment (disease progression).
  - All individual lesions will also be recorded as CR, PR, SD, or PD.
  - Overall survival is the time from the date of first study treatment until death from any cause.

Overall survival and progression-free survival (PFS) will be calculated using the Kaplan-Meier (1958) estimator.(40) Median survival times and their associated 90% confidence intervals will be derived using the method described in Brookmeyer and Crowley (1982).(41)

The percentage of patients with complete responses and the percentage with complete or partial responses will be calculated and confidence intervals derived. The pattern of failures (local or distant) will be summarized. Adverse effects will also be tabulated by type and level of severity. Potential prognostic variables, such as number of lesion sites at baseline, will be examined by fitting Cox (1972) regression models for progression-free and overall survival times.(42) Given the sample size, only univariate analysis will be performed.

- Accrual Rate and Study Duration
  - The estimated accrual will depend on toxicity encountered, but we anticipate enrolling 50-65 patients.
  - We anticipate enrolling 1-3 patients per month.

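### The main response rate pools measurable and bone-scan-only patients, so it depends on case mix, and Table 3 leaves overall response undefined for patients with no measurable lesion

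*Protocol*

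**What the plan says.** Entry: Section 4 states "Unidimensionally measurable disease (based on RECIST) is desirable but not strictly required". The worked example in Section 11.1 describes such a patient. After surgery, whole brain radiation and chemotherapy, CT of the trunk and MRI of the brain are clear, but "bone scan demonstrates residual uptake in the two bone lesions", and the patient is called eligible.

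Scoring: Section 13 states "Lesions seen on bone scan only are not measurable and therefore are evaluated separately" and gives such lesions two outcomes: "Complete response (CR): Disappearance of lesion" and "Stable disease (SD): Persistence of lesion on bone scan". The partial response defined there for all other lesions needs a fall of at least 30% in the summed longest diameters. Table 3 then combines the status of the measurable lesions, the status of the bone-scan-only lesions and the presence of new lesions into one overall response.

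Analysis: Section 16 states "All patients who have met the eligibility criteria will be included in the main analysis of the response rate" and "The percentage of patients with complete responses and the percentage with complete or partial responses will be calculated and confidence intervals derived". It lists eight response categories. Number 3 is stable disease and number 8 is unknown or not assessable. Categories 4 to 8 count as failure to respond. Section 1 makes response rate a secondary endpoint of phase II.

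**The concern.** Entry, scoring and denominator are each fixed in the protocol, and they do not fit together. A patient with measurable lesions becomes a responder through shrinkage. A patient whose only lesions are on bone scan has no diameter to measure and responds, at lesion level, only if the uptake vanishes. The two kinds of patient are then averaged into one percentage.

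The same bone finding is also credited differently. In a patient with measurable lesions, persistent uptake still allows an overall partial response (the Table 3 rows CR with SD, and PR with SD). On its own it is stable disease at best under the lesion-level criteria.

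At stake is the meaning of the reported rate. It describes neither the effect on measurable tumors nor the effect on bone-scan lesions, and it changes with the mix of patients who happen to enrol. Because Table 3 does not cover these patients, whoever codes the data could also change the rate without any change in the data.

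**Working it through.** **Planned figures.** The protocol gives no expected response rate, so there is none to reproduce. The nearest phase II figure is 87% power with 38 patients for a 25% increase in time to progression. A two-sided one-sample z-test at 0.05 returns it: 0.25 × 6.4 = 1.6 months; 3.2/√38 = 0.519; 1.6/0.519 − 1.96 = 1.12; Φ(1.12) = 0.869. Response does not enter this calculation.

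**How the text classifies a patient with no measurable lesion.** Table 3 covers such a patient only when a new lesion appears (PD). Otherwise three codings are possible:

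- The lesion-level result is carried over. Disappearance is CR. Persistence is SD, which is outside failure categories 4–8 but also outside CR+PR.
- The patient is called not assessable (category 8). This counts as failure even if every lesion has disappeared.
- The empty measurable column is entered as CR. The row CR with SD then turns persistent uptake into an overall PR.

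**Effect on the pooled rate.** Let f be the share of bone-scan-only patients, R the CR+PR rate in patients with measurable disease, and c the response rate credited to bone-scan-only patients (under the first coding, their CR rate). Then

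pooled rate = (1 − f) × R + f × c, and shift = pooled − R = f × (c − R).

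The protocol gives none of f, c or R; the values below are assumptions. With R = 50%:

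| f (patients of 38) | c = 0 | c = 20% | c = 40% | c = 60% |
| --- | --- | --- | --- | --- |
| 10% (about 4) | 45% | 47% | 49% | 51% |
| 20% (about 8) | 40% | 44% | 48% | 52% |
| 30% (about 11) | 35% | 41% | 47% | 53% |

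Example: f = 30%, c = 20% gives 0.7 × 0.50 + 0.3 × 0.20 = 0.41. The sign changes where c = R. With R = 30% and f = 20%, c = 0 gives 24% and c = 40% gives 32%.

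**Effect of the gap in Table 3.** The category 8 coding is the column c = 0, a loss of f × R: 5, 10 and 15 points at R = 50%. The third coding, if no new lesion appears, credits every such patient (c = 1). At f = 20% that is 0.8 × 0.50 + 0.2 × 1 = 60%, against 40% under category 8. The same patients thus give rates 20 points apart.

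**Precision if the denominator is restricted.** At a 50% rate the 95% half-width is 1.96 × √(0.25/38) = 0.159 with 38 patients. If 30% are bone-scan-only, 38 × 0.7 = 26.6, about 27 remain, and it is 1.96 × √(0.25/27) = 0.189.

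**The case against.** The plan nowhere claims to estimate response in measurable disease. A rate among all eligible patients is a coherent target for a trial open to any primary site, and a conservative one if these patients respond less often. Evaluable-set and subgroup tables are often left to the statistical analysis plan. Section 16 also has every individual lesion recorded, so the split could be made later. These points limit the weight of the finding but do not remove it. The protocol itself fixes the denominator and the response table, and the table does not say what these patients score.

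A reader might infer that bone-scan-only patients must pull the rate down. The documents do not support that. They can score CR, which counts in both reported percentages, and the shift is downward only if c is below R. That is plausible, since any persistence is SD, but it is not stated.

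A reader might also take the affected group to be all patients with bone disease, and hence large. Section 13 sets apart only lesions seen on bone scan alone. Section 7.1 lists X-ray, CT or MRI of bone-scan abnormalities before therapy and allows PET/CT instead of CT plus bone scan, so a bone lesion seen on one of these is a target lesion. The example in Section 11.1 does not say what dedicated bone imaging showed. Nothing in the protocol fixes f, and even the 10–30% used here is only an illustration.

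Finally, the eligibility checklist may seem to identify the measurable group already. It asks for one count of measurable lesions across CT, MRI, bone scan and PET/CT, so it mixes in the lesions that Section 13 calls non-measurable.

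**Conclusion.** The point holds as a defect of definition. The pooled CR+PR rate depends on the share of bone-scan-only patients, and Table 3 gives them no overall response unless a new lesion appears. The likely direction is downward, but it is not established. With R assumed at 50% and f at 10–30%, the pooled rate is 3 to 15 points below R for c of 0–20% and 1 to 3 points above R for c of 60%. The CR-only percentage could move either way. If these patients are put in category 8, they are failures whatever happened to their lesions.

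The importance is minor. Response rate is a descriptive secondary endpoint with no target or test. Progression-free and overall survival, the sample size and the stated power are unaffected.

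**What to change.** - In Section 16, make the main CR+PR rate that of eligible patients with at least one measurable lesion at baseline, meaning a lesion seen on imaging other than bone scan alone.
- Report bone-scan-only patients separately as disappeared, persisted or new lesion. Keep the all-eligible rate as a supportive figure.
- Add a row to Table 3 for patients with no measurable lesions, so that their overall response is defined and category 8 is kept for missing or inadequate data.
- Split the checklist item so that bone-scan-only lesions are counted apart from measurable ones. The analysis set is then fixed at registration, before any outcome is known.

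The cost is a few lines of text, one form change and one more table row. The statistical cost is a smaller denominator: if 27 rather than 38 patients are measurable, the half-width at a 50% rate grows from about 16 to about 19 points.

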**5.** **EXCLUSION CRITERIA**

1. Other coexisting malignancies or malignancies diagnosed within the previous 3 years with the exception of basal cell carcinoma, cervical carcinoma in situ, and other treated malignancies with no evidence of disease for at least 3 years
2. Uncontrolled intercurrent illness including, but not limited to, ongoing active infection, symptomatic congestive heart failure (CHF), unstable angina pectoris, cardiac arrhythmia, or psychiatric illness/social situations that would limit compliance with the study requirements
3. Patients with clinically significant pulmonary dysfunction, cardiomyopathy, or any history of clinically significant CHF are excluded. The exclusion of patients with active coronary heart disease will be at the discretion of the attending physician.
4. Patients with exudative, bloody, or cytologically malignant effusions are not eligible.
5. Pregnancy or breast feeding (Women of child-bearing potential are eligible, but must consent to using effective contraception during therapy and for at least 3 months after completing therapy)
6. Patients must have no uncontrolled active infection other than that not curable without treatment of their cancer.
7. Prior radiation to target area
8. Patient may not be receiving any other investigational agents during radiotherapy.
9. Prior history of non-inducible bleeding (12/16/09).
10. Requirement for continuation of anticoagulation (defined as Coumadin, lovenox, heparin, plavix, aspirin, NSAIDs or similar drugs) during treatment (12/16/09)

**6. CRITERIA FOR DISCONTINUATION/WITHDRAWAL OF INFORMED CONSENT**

Patients may be discontinued from trial treatment and assessments at any time, at the discretion of the investigator(s). Specific reasons for discontinuing a patient from study treatment are

- objective progression of disease
- patient lost to follow-up (i.e., dropouts)
- adverse events
- protocol non-compliance
- withdrawal of consent

If the reason for withdrawal from the trial is the death of the patient, the two options for categorizing withdrawal are either progressive disease or an adverse event (AE; more than one AE may be documented as a reason for withdrawal). Only one event will be captured as the cause of death. Note that death is an outcome and not an AE.

All deaths that occur within the trial period or within 30 days after administration of the last dose of radiation therapy must be reported primarily for the purposes of serious adverse event (SAE) reporting; however, deaths due unequivocally to progression are not SAEs.

All trial treatment-related toxicities and SAEs must be followed up until resolution.

All patients who have new or worsening grade 3 or 4 laboratory values (Common Terminology Criteria for Adverse Events (CTCAE)) at the time of withdrawal must have additional testing performed, and the results must be recorded in the patients’ medical records. These patients should be followed until the laboratory values have returned to CTCAE grade 1 or 2, or until 30 days after the date of withdrawal (whichever comes first), unless these values are not likely to improve because of the underlying disease. In these cases, the investigators must record their opinions in the patients’ medical records. Laboratory abnormalities should not be reported as adverse events unless any criterion for an SAE is fulfilled, the laboratory abnormality causes the patient to discontinue from the study, or the investigator insists the abnormality should be reported as an AE.

After withdrawal from treatment, unless the patient withdraws consent, follow-up should continue for determination of adverse events, progression-free survival, and overall survival.

**7.** **TREATMENT PLAN: PRE-THERAPY, PERI-THERAPY AND POST-THERAPY ASSESSMENTS**

7.1 Pre-therapy checklist:

- Inclusion/exclusion criteria
- History and physical
- Informed consent
- Pathology confirming cancer
- Documentation of metastatic disease
- Performance status
- Documentation of current medications
- Adverse effect assessment
- CT scan of chest, abdomen, and pelvis
- Bone scan
- Plain X-ray and/or CT and/or MRI of bone abnormality seen on bone scan
- Whole body PET/CT is acceptable replacement for CT scan of chest, abdomen and pelvis and bone scan but is not required
- MRI brain if clinically indicated
- Hematology: CBC (hemoglobin, white blood cell count, platelets) with differential
- Biochemistry: Comprehensive metabolic profile (glucose, sodium, potassium, chloride, carbon dioxide, BUN, creatinine, calcium, total bilirubin, alkaline phosphatase, AST, ALT)
- If suspected to be elevated, obtaining appropriate tumor markers are recommended (PSA, CEA, CA 19-9, EBV viral load, AFP, Beta-HCG)
- Pregnancy test for women of child bearing potential

7.2 Weekly checklist during treatment:

- History and Physical
- Documentation of current medications
- Adverse effect assessment
- Hematology: CBC (hemoglobin, white blood cell count, platelets) with differential

7.3 Supportive Care

- Antiemetics will be ordered at the discretion of the attending physician.
- Mucositis/esophagitis may be ameliorated with sulcrafate or GI cocktail (e.g. Tylenol #3 suspension, bendaryl elixir, Maalox, viscous lidocaine).
- Intravenous hydration is recommended in patients with inadequate oral intake.
- Treatment-related diarrhea will be managed with high-dose loperamide. The recommended dose of loperamide is 4 mg initially (two capsules) then 2 mg after each loose stool, not to exceed 16 mg daily.

7.4 Follow-up checklist: Follow-up visits are to be done every 2 weeks for first 2 months;
 then every 3 months for 1 years; then every 6 months indefinitely

- History and Physical
- Documentation of current medications
- Adverse effect assessment
- CT scan of chest, abdomen, and pelvis (initially 4-6 weeks following completion of radiation therapy to assess response; then every 3 months for first year then every 6 months indefinitely)
- Bone scan (initially 4-6 weeks following completion of radiation therapy to assess response; then every 3 months for first year then every 6 months indefinitely). The bone scan is optional if the patient did not have any evidence of disease on the bone scan upon enrollment into the trial.
- Whole body 18-FDG PET/CT initially 3 months following completion of radiation therapy and every 3 months for the first year and every 6 months thereafter is an acceptable alternative to CT of chest, abdomen and pelvis and bone scan
- Plain X-ray and/or CT and/or MRI of bone abnormality seen on bone scan (if clinically indicated)
- MRI brain if clinically indicated
- Hematology: CBC (hemoglobin, white blood cell count, platelets) with differential
- Biochemistry: Comprehensive metabolic profile (glucose, sodium, potassium, chloride, carbon dioxide, BUN, creatinine, calcium, total bilirubin, alkaline phosphatase, AST, ALT)- (every 3 months for first 2 years then every 6 months indefinitely)
- Tumor markers, if elevated prior to treatment, are recommended
- 18-FDG PET scan every 6 months (optional).

